**Table S9. Association between day 2 LAIV shedding and day 7 pneumococcal density.**

| Variable                             | Change in
log10copies/μl | Standard
Error | P value |
|---------------------------------------------|-------------------------------------|---------------------------|----------------|
| Day 2 high LAIV shedding (vs low shedding)* | +0.036                              | 0.167                     | 0.83           |
| Asymptomatic respiratory virus at day 0     | +0.42                               | 0.172                     | 0.015          |
| Recruitment in 2018 (vs 2017)               | -0.233                              | 0.166                     | 0.16           |
| Age (in months)                             | -0.023                              | 0.009                     | 0.013          |
| Household cooking indoors (vs outdoors)^    | +0.011                              | 0.260                     | 0.97           |

\*high LAIV shedding was defined as having at least one LAIV strain (of three measured) with a RT-PCR cycle threshold (Ct) value equal to or lower than the median Ct value of all LAIV RT-PCR data at day 7. Note lower Ct values denote higher amount of virus. ^Cooking inside (under a roof) compared to cooking using an indoor kitchen. Note 99% of children lived in households where wood/charcoal was primary fuel used to cook regardless of location of cooking.

**Table S10. Adverse events between baseline (day 0) and day 7 of the study**

| Adverse event | LAIV
(n=213) | Control
(n=108) | P value |
|----------------------|-------------------------|----------------------------|----------------|
| Fever                | 32 (15.0%)              | 11 (10.2%)                 | 0.23           |
| Sore throat          | 1 (0.5%)                | 0 (0.0%)                   | 0.48           |
| Chills               | 1 (0.5%)                | 0 (0.0%)                   | 0.48           |
| Muscle/joint pains   | 0 (0.0%)                | 0 (0.0%)                   | -              |
| Headache             | 4 (1.9%)                | 0 (0.0%)                   | 0.15           |
| Epistaxis            | 0 (0.0%)                | 0 (0.0%)                   | -              |
| Nasal congestion     | 7 (3.3%)                | 1 (0.9%)                   | 0.20           |
| Reduced appetite     | 9 (4.2%)                | 8 (7.4%)                   | 0.23           |
| Rhinorrhoea          | 103 (48.4%)             | 25 (23.5%)                 | <0.0001        |
| Rash                 | 6 (2.8%)                | 4 (3.7%)                   | 0.67           |
| Dyspnoea             | 1 (0.5%)                | 0 (0.0%)                   | 0.48           |
| Cough                | 54 (25.4%)              | 19 (17.6%)                 | 0.12           |
| Sputum production    | 5 (2.3%)                | 2 (1.9%)                   | 0.77           |
| Irritability         | 0 (0.0%)                | 1 (0.9%)                   | 0.16           |
| Vomiting             | 8 (3.8%)                | 5 (4.6%)                   | 0.71           |
| Lethargy             | 5 (2.3%)                | 1 (0.9%)                   | 0.37           |
| Diarrhoea            | 13 (6.1%)               | 12 (11.1%)                 | 0.11           |
| Ear pain             | 4 (1.9%)                | 0 (0.0%)                   | 0.15           |

Data are n (%). P values were derived from Chi-square test or Fisher's exact test where appropriate. LAIV=live attenuated influenza vaccine.

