**Table S11. Adverse events between day 7 and day 21 of the study**

| Adverse event | LAIV
(n=213) | Control
(n=108) | P value |
|----------------------|-------------------------|----------------------------|----------------|
| Fever                | 39 (18.3%)              | 15 (13.9%)                 | 0.32           |
| Sore throat          | 3 (1.4%)                | 0 (0.0%)                   | 0.22           |
| Chills               | 0 (0.0%)                | 0 (0.0%)                   | -              |
| Muscle/joint pains   | 0 (0.0%)                | 0 (0.0%)                   | -              |
| Headache             | 4 (1.9%)                | 0 (0.0%)                   | 0.15           |
| Epistaxis            | 0 (0.0%)                | 0 (0.0%)                   | -              |
| Nasal congestion     | 4 (1.9%)                | 1 (0.9%)                   | 0.52           |
| Reduced appetite     | 9 (4.2%)                | 8 (7.4%)                   | 0.23           |
| Rhinorrhoea          | 108 (50.7%)             | 28 (25.9%)                 | <0.0001        |
| Rash                 | 4 (1.9%)                | 2 (1.9%)                   | 0.99           |
| Dyspnoea             | 1 (0.5%)                | 0 (0.0%)                   | 0.48           |
| Cough                | 76 (35.7%)              | 30 (27.8)                  | 0.16           |
| Sputum production    | 2 (0.9%)                | 1 (0.9%)                   | 0.99           |
| Irritability         | 0 (0.0%)                | 1 (0.9%)                   | 0.16           |
| Vomiting             | 4 (1.9%)                | 5 (4.6%)                   | 0.16           |
| Lethargy             | 3 (1.4%)                | 1 (0.9%)                   | 0.71           |
| Diarrhoea            | 14 (6.6%)               | 8 (7.4%)                   | 0.78           |
| Ear pain             | 3 (1.4%)                | 0 (0.0%)                   | 0.22           |

Data are n (%). P values were derived from Chi-square test or Fisher's exact test where appropriate. LAIV=live attenuated influenza vaccine.

[figure not shown]

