(Group D – vaccination and sampling schedule in Table 2), by administration of a single dose of oral azithromycin 28 days prior to receiving LAIV. This timeframe has been chosen based on pilot data from the the Gambia showing significant alternation in the nasopharyngeal microbiome approximately 1 month after single dose oral azithromycin in Gambian children aged 1 – 7 years in mass trachoma treatment campaigns ([name], unpublished, personal communication). These subjects will be matched as closely as possible by pre-antibiotic nasopharyngeal microbiome profile [1], age (24 – 35, 36 – 47, 48 – 59 months) and sex (in that hierarchical preference), in a nested case-control study, to n = 35 children recruited in the main clinical trial. This will be done after all children have been recruited and microbiome sequencing and analysis has been completed. To avoid allocation bias of these controls, an individual in the [name] laboratory blinded to the immunogenicity data will undertake this matching process. In brief, the microbiome profile matching will be performed by first categorizing which of eight described profiles each child's microbiome clusters with depending on the dominant taxa (e.g. *Staphylococcus*, *Streptococcus*, *Moraxella* etc.) as described previously by the [name] group [1].

The day 2 visit window for groups A, B and D is deliberately restrictive to allow both blood and NPS to be taken at a time when peak gene expression changes post-LAIV can be captured. The other visit windows are intentionally liberal to maximize the opportunity to obtain a full set of blood and NPS samples for the purpose of the analysis, whilst in each case, not compromising the scientific objectives they are designed to deliver. However, in each case, the intention will be to obtain the sample on or as close to the day specified as possible. The sampling schedule and associated laboratory assays to be performed on each clinical sample is detailed in Table 3. The procedure to deal with participants who default visit windows is discussed in section 5.4.

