A safety and efficacy study of Nasovac-S was recently completed in the Niakhar region, Senegal, recruiting children aged 24 – 71 months in a randomized, double-blind, placebo-controlled design ([name], XVII International Symposium on Respiratory Viral Infections, Vancouver, CA, 2015). N = 1174 Nasovac-S vaccinated and n = 587 placebo-vaccinated (2:1) children were included. Local reactogenicity (cough, sore throat, runny nose, nasal congestion, ear pain) up to day 7 following vaccination was similar between the groups: with 20.6% and 19.9% of the LAIV and placebo group reporting mild symptoms, 0.4% and 0.2% reporting moderate symptoms and no subjects reporting severe symptoms. Systemic reactogenicity (chills, headache, vomiting, irritability/decreased activity, muscle/joint pain, documented fever, tachypnea) in the same timeframe was rare with 2.7% and 3.2% reporting mild symptoms in LAIV and placebo groups, 0.4% and 0.7% reporting moderate symptoms and 0.1% and 0.0% reporting severe symptoms respectively.

Of the unsolicited adverse events documented as occurring at greater than 1% frequency, 2.3% reported gastrointestinal disturbance (diarrhea, abdominal pain, vomiting, gastroenteritis, enteritis), with these equally balanced between the two groups and no severe symptoms noted. 1.9% were noted to have respiratory, thoracic or mediastinal events (bronchiolitis, nasopharyngitis, oropharyngeal pain, pneumonia, pulmonary congestion, runny nose), with more in the placebo arm (2.7%) than LAIV (1.4%). No life threatening events were noted. Protocol defined wheezing occurred in only one subject (0.2%) in the placebo arm at day 0 – 42 following vaccination and in four children in both the LAIV (0.3%) and placebo (0.7%) groups between day 43 to six months following vaccination.

These data combined provide robust safety data on Nasovac-S in children aged 2 years and over.

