**108 Time windows for the collection of adverse event data**

All adverse events that occur through day 21 post-vaccination with Nasovac-S in groups A, B and D will be assessed and recorded (during scheduled visits at day 2, 7 and 21 after vaccination or if subjects present to the clinical trial site due to illness in between these visits). All adverse events occurring through Day 28 following administration of azithromycin (Group

D only) will be assessed and recorded (at the scheduled visit at day 28 after azithromycin or if subjects present to the clinical trial site due to illness before this visit). Parents/guardians will be advised to contact the study team via telephone or attend the clinical trial site if their child is unwell in between scheduled study visits.

Group C will receive Nasovac-S after NPS has been taken on the day 21 visit, so they are also afforded the same potential benefit of influenza vaccination by participating in the study as groups A, B and D. Given the existing safety data on Nasovac-S (Section 4.1.9), no extra visits will be scheduled for group C specifically for the purpose of gathering adverse event data. Parents/guardians will, however, be advised to contact the study team or bring their child to the health centre if they have any concerns and adverse event data collected, graded and investigated as per AEs in other groups detailed in this section. This will be particularly relevant for post-vaccine AEs for 7 days following vaccination, but aligns with the agreement to assess all study subjects if they are unwell until October 31st of the year of vaccination.

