## **109 Solicited safety data**

All participants will be assessed for local and systemic reactions through 7 days post-vaccination with Nasovac-S. Using a standardized data collection instrument, the following local and systemic reactions will be documented and be graded on magnitude of reaction on the scheduled day 2 visit (for day 0 – 2 symptoms) and day 7 visit (for day 3 – 7 symptoms) following vaccination (see section 7.1.3).

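### Tables S10 and S11 test adverse events between open-label arms whose written enquiry plans differ, so the size of the rhinorrhoea difference is uncertain; separately, the sparse-row P values are not Fisher's exact.

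*Combined protocol and SAP*

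**What the plan says.** Section 108 sets the recording window: "All adverse events that occur through day 21 post-vaccination with Nasovac-S in groups A, B and D will be assessed and recorded", with enquiry "during scheduled visits at day 2, 7 and 21 after vaccination". It has no matching sentence for Group C during its unvaccinated days 0–21. The Group C text there, "no extra visits will be scheduled for group C specifically for the purpose of gathering adverse event data", concerns the period after that group's own dose at day 21.

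Section 109 provides a standardised form to grade local and systemic reactions after vaccination, completed "on the scheduled day 2 visit (for day 0 – 2 symptoms) and day 7 visit (for day 3 – 7 symptoms"). Section 21 adds: "The day 2 visit window for groups A, B and D is deliberately restrictive". Table 1 of the protocol shows no day 2 visit for Group C, only days 0, 7 and 21.

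Section 107 is broader. It says the study has no defined safety endpoints, and that adverse events will be gathered passively and by asking at scheduled visits, without limiting this to any group. Section 110 has solicited reactions still present at day 7 recorded as adverse events.

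Section 21 states that investigators are not blinded after allocation, and the control group is unvaccinated. The planned analyses include no between-arm adverse-event test. The supplement's "Table S10. Adverse events between baseline (day 0) and day 7 of the study" and Table S11 nevertheless give P values, with the footnote "P values were derived from Chi-square test or Fisher's exact test where appropriate".

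**The concern.** The events in these tables are mostly symptoms that a parent has to notice and report. If one arm is asked more often, over shorter recall, with a structured form, and knows it was vaccinated, more reports are expected in that arm whatever the vaccine does. On the written schedule LAIV families are asked at days 2 and 7 in the first week and control families at day 7. Neither table mentions open allocation or how each arm was asked.

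At stake is the one striking safety contrast, rhinorrhoea at P<0.0001 in both tables. A reader may take its size at face value. The footnote also tells the reader that sparse rows were tested exactly, which the printed values do not bear out.

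**Working it through.** **Inputs.** Counts and printed P values come from Tables S10 and S11 (LAIV n=213, control n=108, total 321); visit schedules come from Table 1 and sections 107 to 110.

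**1. Rhinorrhoea, days 0–7.** 103/213 = 48.4%. 25/108 = 23.1%; the table prints 23.5%. Uncorrected chi-square P = 1.3×10⁻⁵ and Fisher P = 1.2×10⁻⁵, so the printed <0.0001 is reproduced.

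Difference = 0.4836 − 0.2315 = 0.2521. SE = √(0.4836×0.5164/213 + 0.2315×0.7685/108) = 0.0531. 95% CI = 0.2521 ± 1.96×0.0531, or 14.8 to 35.6 points.

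**2. Rhinorrhoea, days 7–21, with no extra scheduled visit in either arm.** 108/213 = 50.7% and 28/108 = 25.9%. Difference = 24.8 points, SE = 0.0543, 95% CI 14.1 to 35.4, P = 2.2×10⁻⁵. The gap is almost the same as in step 1.

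**3. How unequal would enquiry have to be?** The documents do not give the reports found only at day 2, so a corrected effect cannot be computed. As an assumption, let control enquiry have caught a fraction s of what LAIV enquiry caught on days 0–7. The adjusted control count is 25/s.

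| s | Adjusted control rate | P |
|---|---|---|
| 0.9 | 25.7% | 0.0001 |
| 0.8 | 28.9% | 0.0009 |
| 0.7 | 33.1% | 0.009 |
| 0.6 | 38.6% | 0.10 |
| 0.5 | 46.3% | 0.73 |

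P first reaches 0.05 at a control count of 40, so s = 25/40 = 62.5%. Seen from the other arm, 32 of the 103 LAIV reports (31%) would have to be removed for P ≥ 0.05. To reach the control rate, 103 − 213×25/108 = 53.7 (52%) would have to go.

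**4. Sparse rows.** The smallest expected count is (events in row) × 108/321, for example 4×108/321 = 1.35. For 4 v 0, uncorrected chi-square = 321×(4×108)²/(213×108×4×317) = 2.05, P = 0.152; Fisher gives 0.30; the table prints 0.15. Of 31 testable rows, 21 have an expected count below 5 (11 in Table S10, 10 in Table S11):

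| Table: row (LAIV v control) | Min. expected | Printed | Chi-square | Fisher |
|---|---|---|---|---|
| S10: sore throat, chills, dyspnoea (1 v 0) | 0.34 | 0.48 | 0.476 | 1.00 |
| S10: headache, ear pain (4 v 0) | 1.35 | 0.15 | 0.152 | 0.30 |
| S10: nasal congestion (7 v 1) | 2.69 | 0.20 | 0.200 | 0.28 |
| S10: rash (6 v 4) | 3.36 | 0.67 | 0.666 | 0.74 |
| S10: sputum (5 v 2) | 2.36 | 0.77 | 0.774 | 1.00 |
| S10: irritability (0 v 1) | 0.34 | 0.16 | 0.160 | 0.34 |
| S10: vomiting (8 v 5) | 4.37 | 0.71 | 0.708 | 0.77 |
| S10: lethargy (5 v 1) | 2.02 | 0.37 | 0.374 | 0.67 |
| S11: sore throat, ear pain (3 v 0) | 1.01 | 0.22 | 0.215 | 0.55 |
| S11: headache (4 v 0) | 1.35 | 0.15 | 0.152 | 0.30 |
| S11: nasal congestion (4 v 1) | 1.68 | 0.52 | 0.515 | 0.67 |
| S11: rash (4 v 2) | 2.02 | 0.99 | 0.987 | 1.00 |
| S11: dyspnoea (1 v 0) | 0.34 | 0.48 | 0.476 | 1.00 |
| S11: sputum (2 v 1) | 1.01 | 0.99 | 0.991 | 1.00 |
| S11: irritability (0 v 1) | 0.34 | 0.16 | 0.160 | 0.34 |
| S11: vomiting (4 v 5) | 3.03 | 0.16 | 0.158 | 0.17 |
| S11: lethargy (3 v 1) | 1.35 | 0.71 | 0.713 | 1.00 |

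All 21 printed values equal the uncorrected chi-square after rounding. None equals Fisher.

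**The case against.** A reader might infer that controls had no planned collection at all. The documents do not support that. Section 107 plans questions at scheduled visits for everyone, and controls attend at days 7 and 21. Section 60 refers to Appendix 1 for each group's schedule; only the Group D row is in the text available, so direct enquiry in Groups A to C cannot be checked. Both arms are reported on one list of 18 events, including rows that are zero in both. That list differs from the solicited list: it has epistaxis, rash and diarrhoea and lacks nasal discomfort and tachypnoea. This suggests a common checklist but does not prove one.

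A reader might also blame the day 2 enquiry for the excess. The near-identical gap in Table S11 argues against that as the main cause. Diarrhoea, reduced appetite, vomiting, rash and irritability are each more frequent in controls in Table S10, which argues against general under-reporting there, although of these only vomiting and irritability are on the solicited list.

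The placebo-controlled trials in section 42 tempt one to call the excess an artefact. In Senegal local reactogenicity "up to day 7 following vaccination was similar between the groups" (mild symptoms 20.6% v 19.9%), and in Bangladesh runny nose or congestion was 20.7% v 22.7%. These are different composites in other populations. Section 6 also reports mild increases in runny nose with another LAIV, so a true effect is plausible.

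Finally, the tables are descriptive and make no causal claim, so there is none to withdraw.

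These points stand, and they limit the conclusion to uncertainty about size. They do not make Table S11 a clean check: it is equally open-label, and section 110 carries reactions present at day 7 forward after vaccination, with no written counterpart in unvaccinated controls. Nor do they touch the sparse-row error.

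**Conclusion.** The point holds as a reporting and interpretation issue. Day 0–7 ascertainment is potentially unequal and was unblinded, so 25.2 points (14.8 to 35.6) should not be read as a precise vaccine effect. Open-label reporting may affect both tables, and carry-over of reactions may affect Table S11. The documents do not show that the excess is spurious. Under the assumed single capture fraction, control enquiry would have had to catch no more than about 62% of what LAIV enquiry caught for P to reach 0.05.

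The arithmetic errors are certain, taking an expected count below 5 as the usual threshold for Fisher's test, since the footnote does not define one. Counts of 0.34 would fail any customary threshold. Twenty-one P values and one percentage need correcting. No row crosses 0.05 and the rhinorrhoea result is unchanged.

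**What to change.** 1. Recalculate every row with an expected count below 5 by Fisher's exact test, and correct 23.5% to 23.1%.
2. In sections 108 and 109, apply the same symptom form by direct enquiry to Group C at its existing day 7 and day 21 visits. For the completed data, state whether this was done.
3. Give risk differences with 95% CIs, labelled open-label and parent-reported, in both tables. Note the possible carry-over in Table S11.
4. Add a sensitivity analysis over the same recall window in both arms. For example, exclude LAIV events reported only at day 2 and restrict control events to days 3–7, if onset dates were recorded, with one rule for symptoms that began earlier and persisted. A comparison of whatever was recorded at the day 7 visit is not a substitute: under section 109 the LAIV report there covers days 3–7, while a control's first report would cover days 0–7.

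The cost is re-tabulation, plus one form at visits already scheduled. No visits are added. The downside is that days 0–2 symptoms have no comparator in the sensitivity analysis.

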**Table S11. Adverse events between day 7 and day 21 of the study**

| Adverse event | LAIV
(n=213) | Control
(n=108) | P value |
|----------------------|-------------------------|----------------------------|----------------|
| Fever                | 39 (18.3%)              | 15 (13.9%)                 | 0.32           |
| Sore throat          | 3 (1.4%)                | 0 (0.0%)                   | 0.22           |
| Chills               | 0 (0.0%)                | 0 (0.0%)                   | -              |
| Muscle/joint pains   | 0 (0.0%)                | 0 (0.0%)                   | -              |
| Headache             | 4 (1.9%)                | 0 (0.0%)                   | 0.15           |
| Epistaxis            | 0 (0.0%)                | 0 (0.0%)                   | -              |
| Nasal congestion     | 4 (1.9%)                | 1 (0.9%)                   | 0.52           |
| Reduced appetite     | 9 (4.2%)                | 8 (7.4%)                   | 0.23           |
| Rhinorrhoea          | 108 (50.7%)             | 28 (25.9%)                 | <0.0001        |
| Rash                 | 4 (1.9%)                | 2 (1.9%)                   | 0.99           |
| Dyspnoea             | 1 (0.5%)                | 0 (0.0%)                   | 0.48           |
| Cough                | 76 (35.7%)              | 30 (27.8)                  | 0.16           |
| Sputum production    | 2 (0.9%)                | 1 (0.9%)                   | 0.99           |
| Irritability         | 0 (0.0%)                | 1 (0.9%)                   | 0.16           |
| Vomiting             | 4 (1.9%)                | 5 (4.6%)                   | 0.16           |
| Lethargy             | 3 (1.4%)                | 1 (0.9%)                   | 0.71           |
| Diarrhoea            | 14 (6.6%)               | 8 (7.4%)                   | 0.78           |
| Ear pain             | 3 (1.4%)                | 0 (0.0%)                   | 0.22           |

Data are n (%). P values were derived from Chi-square test or Fisher's exact test where appropriate. LAIV=live attenuated influenza vaccine.

[figure not shown]

**Figure S1. Distribution of *S. pneumoniae* density data at different timepoints.**

[figure not shown]

## **List of abbreviations**

|        |                                            |
|--------|--------------------------------------------|
| AE     | Adverse event                              |
| AEFI   | Adverse Event Following Immunization       |
| ALRI   | Acute lower respiratory infection          |
| CRF    | Case Report Form                           |
| CSR    | Class switch recombination                 |
| DCF    | Data Clarification Form                    |
| DMP    | Data Management Plan                       |
| EC     | Ethics Committee                           |
| EID    | Egg Infective Dose                         |
| ELISA  | Enzyme-Linked Immunosorbent Assay          |
| EPI    | Expanded Programme on Immunization         |
| FSFV   | First Subject First Visit                  |
| FW     | Field Worker                               |
| GCLP   | Good Clinical Laboratory Practice          |
| GCP    | Good Clinical Practice                     |
| HA     | Haemagglutinin                             |
| HI     | Haemagglutinin Inhibition                  |
| ICD    | Informed Consent Document                  |
| ICH    | International Conference on Harmonization  |
| IFITM3 | Interferon-induced transmembrane protein-3 |
| IgA    | Immunoglobulin A                           |
| IgG    | Immunoglobulin G                           |
| IIV    | Inactivated Influenza Vaccine              |
| ILI    | Influenza-like Illness                     |
| LAIV   | Live Attenuated Influenza Vaccine          |
| LMIC   | Low and Middle Income Countries            |
| LSFV   | Last Subject First Visit                   |
| MDV    | Master Donor Virus                         |
| mL     | Millilitre                                 |
| MRC    | Medical Research Council                   |
| NA     | Neuraminidase                              |
| NPS    | Nasopharyngeal Swab                        |
| OTU    | Operational Taxonomic Unit                 |
| PCR    | Polymerase Chain Reaction                  |
| pCRF   | Paper Case Report Form                     |
| PCV    | Pneumococcal-Conjugate Vaccine             |
| PD     | Protocol Deviation                         |
| PI     | Principal Investigator                     |
| pTfh   | Peripheral T-follicular helper             |
| QA     | Quality Assurance                          |

|         |                                                          |
|---------|----------------------------------------------------------|
| QC      | Quality Checked                                          |
| RCT     | Randomized Controlled Trial                              |
| rRT-PCR | Realtime Reverse Transcriptase Polymerase Chain Reaction |
| SAE     | Serious Adverse Event                                    |
| SAGE    | Strategic Advisory Group of Experts                      |
| SAP     | Statistical Analysis Plan                                |
| SARI    | Severe Acute Respiratory Illness                         |
| SDV     | Source Data Verification                                 |
| SIIL    | Serum Institute of India, Pvt. Limited                   |
| SOP     | Standard Operating Procedure                             |
| SSPs    | Study Specific Procedures                                |
| SST     | Serum Separation Tube                                    |
| TMF     | Trial Master File                                        |
| UAT     | User Acceptance Testing                                  |
| UK      | United Kingdom                                           |
| URT     | Upper Respiratory Tract                                  |
| US      | United States                                            |
| WHO     | World Health Organization                                |

